## Background

Schizophrenia and related disorders remain associated with relatively poor psychosocial outcomes [1]. Impaired insight has been reported to be the strongest predictor of this poor outcome in psychotic disorders [2]. However, the effect size of previous treatments on insight changes in psychotic disorders has been relatively small to date [3, 4], which may have been the result of not tackling the actual underpinnings of insight in psychosis.

Several theories have been proposed to explain what underlies ‘lack of insight’ in schizophrenia spectrum disorders. First, lack of insight could be viewed as having a function in terms of being protective or preserving self-esteem, i.e., a denial mechanism [5]. Second, lack of insight may also be considered as a primary symptom of the disorder [6]. Third, the neurocognitive basis of insight was in part supported by a meta-analysis [7], which also suggested that other variables, namely metacognition, which was defined as ‘the ability to think of one’s and others’ thinking’ [8, 9], may affect insight. Indeed, patients with schizophrenia have been reported to show metacognitive deficits [10, 11] and poorer metacognitive performance is linked with impaired insight in schizophrenia [12]. Metacognitive training (MCT) may therefore improve insight, which should also have a positive impact on clinical outcomes.

MCT was first developed by Steffen Moritz and Todd Woodward [13] and is available at no cost at: http://www.uke.de/mct. Since then, one systematic review [14] and four meta-analyses [15–18] have replicated the positive effects of MCT on positive symptoms, particularly delusions, when compared with ‘treatment as usual’ (TAU), although one meta-analysis [19] failed to show such an association. However, to the best of our knowledge no definitive randomised clinical trial (RCT) using MCT has considered insight as primary outcome to date, although three previous RCTs found other non-MCT metacognitively oriented therapies to improve insight in first-episode psychosis [20] and schizophrenia [21, 22].

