### Statistical analysis

Participants’ data will be analysed at the end of the study on an intention-to-treat (ITT) basis, thus including all patients with baseline information available. Imputation methods will be used to estimate missing values. All the analyses will be performed with the Statistical Package for Social Science version 25.0 (SPSS Inc., Chicago, IL, USA).

First, demographic and clinical characteristics of groups (MCT and controls), including insight measures, will be compared at baseline so parametric and non-parametric tests will be used as appropriate. Also, for descriptive purposes, between-arm completion rates differences will be analysed at the end of the study.

Second, in order to investigate the primary outcome of the study, namely insight changes over the trial period, univariate analysis of covariance (ANCOVA) models will examine between-group differences (MCT and controls) in the SAI-E and BCIS total and subtotal scores changes from T0 to T1 and from T0 to T2 (as the dependent variable), whilst adjusting for baseline data. Hence, the effects of treatment (independent of time) and treatment group allocation*time interactions on insight changes will be investigated. We will also explore within-group scores changes between T0, T1 and T2. Specifically, we will estimate effect sizes (Cohen’s *d*) and the corresponding 95% confidence intervals (CI) from the imputed datasets for between- and within-group insight scores changes. In accordance with Cohen’s conventions [52], effect sizes will be classified as ‘small’ (*d < 0.2),* ‘medium’ *(d* = 0.2–0.5) or ‘large’ (*d* > 0.8). Due to multiple testing and the subsequent risk of type I error, results will be adjusted using Bonferroni correction.

Third, for the secondary outcomes evaluated with continuous variables, i.e., symptom severity (PANSS and CDSS) and functioning (GAF, SDLS and WHODAS), analogous ANCOVA models will be used. For those binary secondary outcomes, namely suicidal behaviour and readmissions, survival analyses, i.e., multivariable Cox regression models [53], will model time to the outcome event (i.e., first suicidal event or hospital admission, respectively) or the censoring date as appropriate, whilst adjusting for baseline variables.

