#### Power calculations and estimation of sample size

Given that the mean SAI-E score for psychosis patients is 13/28 with a standard deviation of around 6 [32, 35], a difference of 2 points (e.g., 13 vs. 15) between groups (e.g., MCT vs. controls), which is considered to be clinically meaningful [26], is equivalent to an effect size of 0.33 with a two-tailed alpha significant level set at 5%. Under these assumptions, for reaching a sufficient statistical power of β = 80% at the end of the study, we will need *n* = 63 subjects in each arm, that is, a total sample size of *N* = 126 patients, who will be analysed at the end of the study on an intention-to-treat (ITT) basis. Attrition rates in previous RCTs investigating MCT effects on symptoms were low (approximately 10%) [18]. However, since we will follow-up patients over a more prolonged period (1 year) we have conservatively assumed a much higher drop-out rate of 50%. Under this assumption, the study will be carried out with an initial sample size of *N* = 252 patients, i.e., *n* = 126 participants in each group/arm at the study inception, which will also allow both ITT and ‘per protocol’ analyses with sufficient power. See the CONSORT flow chart in Fig. 1 for details.

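### The effect-size labels leave d above 0.5 and up to 0.8 without a class and label effects below 0.5 one class too high; this affects only how results are described

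*Protocol article*

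**What the plan says.** In the protocol article, Statistical analysis, the paragraph on the primary outcome sets out ANCOVA models for changes in SAI-E and BCIS total and subtotal scores. It then adds a standardised summary: "we will estimate effect sizes (Cohen’s *d*) and the corresponding 95% confidence intervals (CI) from the imputed datasets for between- and within-group insight scores changes". The labelling rule follows: "In accordance with Cohen’s conventions [52], effect sizes will be classified as" "small’ (*d < 0.2),* ‘medium’ *(d* = 0.2–0.5) or ‘large’ (*d* > 0.8". No other section adds a class or amends these limits.

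Two other places bear on the rule. Power calculations and estimation of sample size states that "the mean SAI-E score for psychosis patients is 13/28 with a standard deviation of around 6", and that "a difference of 2 points (e.g., 13 vs. 15) between groups" "is equivalent to an effect size of 0.33". The Background says of earlier work that "the effect size of previous treatments on insight changes in psychotic disorders has been relatively small to date".

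**The concern.** A labelling rule fixed in advance should give every possible estimate exactly one label, so that the wording cannot be chosen after the data are seen. This rule falls short in two ways.

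- **A gap.** Estimates above 0.5 and up to 0.8 have no label. The text alone shows this.
- **A shift.** The rule claims to follow Cohen's conventions. As commonly used, these take 0.2, 0.5 and 0.8 as the benchmarks for small, medium and large. The protocol keeps the three numbers but makes 0.2 the ceiling of small and 0.5 the ceiling of medium, while 0.8 stays the floor of large. Mixing ceilings and floors is also what opens the gap.

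At stake is how the co-primary effect sizes are put into words. A near-zero effect could be called small and a conventionally small one medium, while a moderately large one would have no agreed label.

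**Working it through.** **Inputs.** Limits 0.2, 0.5 and 0.8 (Statistical analysis). SAI-E score SD about 6, target difference 2 points, design effect 0.33, 63 per arm for analysis and 126 per arm at entry (Power calculations). The reading of Cohen's benchmarks is general statistical knowledge; the cited reference was not consulted.

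**1. Design effect.** 2 / 6 = 0.333, which reproduces the stated 0.33.

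**2. Coverage of the d scale.**

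| d | Label in the protocol | Label with 0.2, 0.5 and 0.8 as lower limits |
|---|---|---|
| below 0.2, including 0 | small | negligible |
| 0.2 to below 0.5, including 0.33 | medium | small |
| exactly 0.5 | medium | medium |
| above 0.5, below 0.8 | none | medium |
| exactly 0.8 | none | large |
| above 0.8 | large | large |

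The rule is also silent on sign. Read literally, any negative d is small, because it lies below 0.2. This matters for subtotal scores: BCIS self-certainty is subtracted in the composite index, so improvement there is a fall in score.

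**3. The unlabelled band in SAI-E points.** The answer depends on which SD standardises d, and the protocol does not say. Its SD of 6 describes the score, whereas the rule applies d to changes. If the SD is 6 at both times and the baseline–follow-up correlation is r (an assumption; none is given), the SD of change is 6 × √(2(1 − r)).

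| Standardiser | SD | 0.5 × SD | 0.8 × SD | d for 2 points |
|---|---|---|---|---|
| Score SD | 6.0 | 3.0 | 4.8 | 0.33 |
| Change SD, r = 0.75 | 4.2 | 2.1 | 3.4 | 0.47 |
| Change SD, r = 0.5 | 6.0 | 3.0 | 4.8 | 0.33 |
| Change SD, r = 0.3 | 7.1 | 3.6 | 5.7 | 0.28 |

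In all four rows the target difference of 2 points lies between 0.2 and 0.5, so the protocol's rule calls it medium.

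**4. How often an estimate would fall in the gap.** A normal approximation for the between-group d is used, with SE = √(2/n + d²/(4n)) for n per arm. For d = 0.333 and n = 63, SE = √(0.03175 + 0.00044) = 0.179. The chance of an estimate between 0.5 and 0.8 is then Φ(2.60) − Φ(0.93), about 17%.

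| True d | 63 per arm | 126 per arm |
|---|---|---|
| 0.33 | 17% | 9% |
| 0.5 | 45% | 49% |
| 0.6 | 57% | 72% |

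Only 0.33 comes from the protocol; 0.5 and 0.6 are illustrations.

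**The case against.** The strongest reply is that nothing inferential depends on the label. The primary analysis is ANCOVA with Bonferroni correction, and d is to be reported with its 95% confidence interval, so a reader sees the number beside any adjective. No success criterion uses the classes, and the sentence may be a typing slip. This stands, and it sets the severity.

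Three stronger readings are tempting but not supported.

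- **That the labels would manufacture an advance over earlier treatments.** A reader might infer this from the Background, where earlier effects on insight are called relatively small. The protocol gives no d for those effects and does not say that the description used these bands. If they were below 0.2, this rule would call them small as well, and no contrast would arise.
- **That every result will be mislabelled or unclassifiable.** It depends on the estimate. Values above 0.8, and exactly 0.5, receive the conventional label. The power section itself does not call 0.33 medium; that label appears only when the rule is applied to it.
- **That the gap is a fixed 3.0 to 4.8 SAI-E points.** That holds only for a standardiser of 6. No corresponding figure can be given for the BCIS, because the protocol states no SD for it.

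The reply does not remove the defect itself. The article states the rule in full and states it incompletely, so this is not detail left to a fuller plan.

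**Conclusion.** The point holds as a minor reporting defect. The gap follows from the protocol's own words. The shift rests on the common reading of Cohen's benchmarks, and the protocol's use of 0.8 as a lower limit for large is consistent with that reading. Followed as written, the rule labels effects below 0.5 one class too high, including the design effect, and cannot label effects above 0.5 and up to 0.8. Any statement of the gap in SAI-E points must name its standardiser. The consequence is confined to the description of the co-primary effect sizes; tests, confidence intervals, alpha and sample size are untouched.

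**What to change.** Replace the classification sentence with bands that adjoin and do not overlap, applied to the absolute value of d with the direction stated separately:

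- below 0.2: negligible
- 0.2 to below 0.5: small
- 0.5 to below 0.8: medium
- 0.8 or more: large

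If d is also expressed in SAI-E points, state which SD is used, that of the score or that of the change. Make the edit before results are known. It needs no new data and leaves the analysis unchanged; the only cost is that some results will carry a less favourable label.

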### Outcome measures

#### Co-primary outcomes

Insight is the primary outcome of this RCT and both clinical and cognitive insight will be considered.
*Clinical insight* will be measured with the Spanish version [33] of the Schedule for Assessment of Insight, expanded version (SAI-E) [26]. The SAI-E takes the form of a semi-structured interview which enquires about different aspects of insight and provides scores on three insight dimensions in line with David’s model [23] - illness recognition, symptom relabeling, treatment compliance - and a total insight score. The scale was found to be easily applicable in routine clinical practice [34] and good to excellent inter-rater reliability was reached, with total insight scores intra-class correlations coefficients ranging from 0.92 to 0.98 (*p* < 0.001) [35]. [name] received training from the scale author ([name]) and they both co-led the validation study of the SAI-E Spanish version [33], which will be used in this RCT.*Cognitive insight* will be assessed by the Spanish version [36] of the Beck Cognitive Insight Scale (BCIS) [10], which is a 15-item self-administered scale which evaluates self-reflectiveness (9 items) and self-certainty (6 items). A composite index can thus be calculated by subtracting self-certainty from self-reflectiveness. Internal consistency was found to be acceptable (Cronbach’s α = 0.60–0.68) [37].

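### Single-step Bonferroni for the insight tests is valid but dominated by Holm's step-down; the swap is cheap and its gain is small

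*Protocol article*

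**What the plan says.** The Co-primary outcomes section states: "Insight is the primary outcome of this RCT and both clinical and cognitive insight will be considered". It lists a total and three dimensions for the SAI-E, and a composite and two subscales for the BCIS.

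The Statistical analysis section compares the arms by ANCOVA on "SAI-E and BCIS total and subtotal scores changes from T0 to T1 and from T0 to T2". The same paragraph also covers group-by-time interactions, within-group changes, and effect sizes with ordinary 95% confidence intervals. It ends by saying that, because several tests are made, "results will be adjusted using Bonferroni correction". No step-down or hierarchical procedure is named, and the number of tests in the family is not given.

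The sample-size section uses a "two-tailed alpha significant level set at 5"%, undivided, with a 2-point SAI-E difference and an SD of about 6.

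**The concern.** Bonferroni holds every contrast to 0.05/m, however many of the others have already been rejected. Controlling the family-wise error at 5% does not require this. After one rejection at 0.05/m, the remaining m − 1 contrasts can be tested at 0.05/(m − 1), and so on. That is Holm's procedure. It makes no assumption about how the tests are correlated, so it applies to totals tested alongside their own subscales at two visits.

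The second and later rejections matter in this trial. It names clinical and cognitive insight as co-primary, wants to look at the insight dimensions individually (Methodological issues), and tests at both T1 and T2. A real effect on one dimension or visit could miss the Bonferroni threshold and pass Holm's, with family-wise error still held at 5%.

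**Working it through.** **Inputs from the protocol.** Scores: SAI-E total + 3 dimensions = 4; BCIS composite (read as its total) + 2 subscales = 3. Contrasts: (4 + 3) × 2 visits = 14. Effect size: 2/6 = 0.33. Per arm: 63 analysed, 126 randomised.

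**Assumptions, not in the protocol.** All 14 contrasts form one family. Test statistics correlate 0.6 between visits, 0.4 within a scale and 0.2 between scales, with the product used for different scores at different visits.

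**The plan's own figure.** The protocol gives no power figure that allows for multiplicity. Its 63 per arm is not reproduced by its stated inputs. A two-sided 5% test with 80% power needs 2 × (1.960 + 0.842)² / (2/6)² ≈ 142 per arm. At 63 per arm the power is about 46% before any correction. That is a separate matter, but it sets the scale here.

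**Step 1: thresholds.** Bonferroni tests all 14 at 0.05/14 = 0.00357. Holm orders the p-values and tests at 0.05/14, 0.05/13 = 0.00385, 0.05/12 = 0.00417, …, 0.05, stopping at the first failure. The first step is the same, so the chance of at least one rejection is the same. Every later threshold is larger, so no Bonferroni rejection is lost.

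**Step 2: Bonferroni power for one contrast.** Power ≈ Φ(d√(n/2) − z), with z = 2.914 for two-sided 0.00357.
- n = 126: 0.33 × √63 = 2.619; Φ(−0.295) ≈ 38%.
- n = 63: 0.33 × √31.5 = 1.852; Φ(−1.062) ≈ 14%.

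**Step 3: Holm power for the SAI-E total at T2**, by simulation (400,000 sets of 14 correlated z-statistics, d = 0.33 on the scores that respond, zero on the rest):

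| Scores that respond | 126 per arm, Bonferroni → Holm | 63 per arm, Bonferroni → Holm |
|---|---|---|
| Both totals only | 38.4% → 39.6% | 14.4% → 14.8% |
| All SAI-E scores | 38.4% → 41.7% | 14.4% → 15.5% |
| All scores | 38.4% → 47.2% | 14.4% → 16.7% |

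If only the totals respond, the expected number of significant contrasts goes from about 1.57 to 1.63 with 126 per arm, and from 0.61 to 0.63 with 63. With no effect anywhere, the family-wise error is about 4.4% for both methods. In no simulated set did Bonferroni reject a contrast that Holm retained.

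**Step 4: smaller families.** The protocol does not count the family, so smaller ones were also tried (d = 2/6 on every endpoint, common correlation 0.3, 126 per arm). With two tests, power to show both goes from 47.5% to 59.1%, and power to show at least one stays at 84.1%. With four tests, power to show all four goes from 18.7% to 39.2%. Holm's advantage therefore does not depend on assuming 14 contrasts, though its size does depend on how many endpoints respond.

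**The case against.** The strongest objection is that nothing here is an error. Bonferroni controls the error the plan names and contradicts no other section. Choosing a valid correction over a sharper one is a question of efficiency. That stands, and it limits the severity. It does not make the choice a good one, because the alternative uses the same p-values and cannot lose a result.

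Second, the gain is small where the protocol expects to analyse, at 63 per arm, and nil for the first rejection. That also stands.

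Third, Bonferroni gives simple simultaneous intervals and Holm does not. So a reader who infers that power is given away for nothing goes too far. The plan, however, describes its intervals as ordinary 95% ones and makes no use of that advantage.

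Two other readings are tempting. One is that Holm would raise the expected number of significant contrasts by about a fifth, for example from 3.7 to 4.4 with 126 per arm. Figures of that order appear only if the subscales also respond, at about 0.8 of the effect on the totals; nothing in the protocol supports assuming that. The other is that type I error is uncontrolled as written. It is not.

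Finally, an article may leave detail to a fuller plan. Here the article does name the correction, so the choice itself can be reviewed.

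**Conclusion.** The point holds as a cheap improvement of low severity. Single-step Bonferroni is valid and uniformly dominated by Holm for these tests. With 126 per arm, power for the SAI-E total at T2 rises by about 1 point if only the totals respond, 3 if all SAI-E scores do, and 9 if all scores do. With 63 per arm the rise is about 0.4 to 2.3 points. These sizes rest on the assumed family of 14, d = 0.33 and the assumed correlations. The dominance and the unchanged chance of a first rejection need none of these assumptions. A reader might infer that the swap makes the trial adequately powered. It does not: the gap between 63 and about 142 per arm remains.

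**What to change.** Replace the Bonferroni sentence in the Statistical analysis section by: *Family-wise error over the between-arm SAI-E and BCIS total and subtotal contrasts at T1 and T2 is controlled at two-sided 5% by Holm's step-down procedure; within-group changes and group-by-time interactions keep the Bonferroni correction.*

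This names the contrasts, without which Holm cannot be run, and says what happens to the other analyses in that paragraph. If the sponsor intends the present sentence to treat all of them as one family, Holm can be run over that whole set with the same guarantee.

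The cost is one sentence and a ranking of p-values already computed, settled before the arms are compared. The downside is that there is no simple simultaneous interval to match Holm. The ordinary 95% intervals can stay as planned, and Bonferroni-level intervals, if wanted, remain valid but slightly conservative.

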### Assessments

Participants will be assessed at three timepoints: i) T0: at baseline; ii) T1: after treatment; iii) T2: at 1-year follow-up. Data on different variables will be collected at each of these assessments, which is detailed in the SPIRIT flowchart shown in Table 1, below.

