### Outcome measures

In addition to the primary outcome of this RCT, namely insight, we will consider several clinical outcomes, both positive and negative, such as symptom severity, functioning, readmissions and suicidal behaviour, thus testing the so-called ‘Insight Paradox’ [54]. Although the positive impact of MCT on symptoms has been established [14–18], most of previous RCTs included in these meta-analyses compared MCT with TAU. Therefore, not only this RCT may replicate this, but also by comparing the MCT group with an active intervention control group, if the above positive effect was shown, this would provide further support for the benefits of MCT on symptoms. Beyond and above the effects of MCT on symptoms, functioning will be comprehensively examined, consistently with current guidelines focused on recovery as main outcome measure [55]. Also, functioning will be evaluated with novel methodology such as EMA, which has not been sufficiently researched in psychosis patients.

However, insight was also linked with negative outcomes. In particular, insight was thought to lead to depression, hopelessness and suicidality, which is known as the demoralization syndrome [56, 57] or ‘Insight Paradox’ [54]. However, recent research did not show a ‘direct’ relationship between insight and suicidality in first-episode psychosis, which was due to the confounding effects of previous suicide attempts and depression on such an association [32]. The question therefore arises, i.e., whether an insight improving intervention (such as MCT, which is to be tested in this trial) may reduce suicide risk (and improve mood) in psychosis, which will be properly investigated in this RCT. In addition to suicidal behaviour-related outcomes, we will test whether MCT can reduce admissions over the trial period, which is of relevance from a cost-effectiveness perspective [58].

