### Strengths and weaknesses

At this pre-recruitment stage, we already acknowledge that this RCT has strengths and weaknesses. In particular, we intend to recruit a large sample size of SSD patients who will also be representative of our local population since most of our psychosis patients receive mental healthcare in our clinic with the exception of a tiny proportion in either primary care or in the private sector. As detailed above, controls will also attend a weekly ‘therapeutic-like’ group, thus controlling for the effect of attending a group, which will represent a more challenging test for MCT. In addition, the main authors of MCT, Steffen Moritz and Todd Woodward, will not get directly involved in this RCT, thus avoiding allegiance-related biases. Of course, the vast majority, if not all, patients are expected to continue taking medication as prescribed, particularly antipsychotics, so medication-related variables will be included in secondary analyses since they may affect the effect of MCT on insight.

However, this is a RCT so participants are required to give consent and complete a comprehensive set of assessments. Hence, those with the lower levels of cooperativeness, and therefore with poorer insight, are not likely to take part in this study, which may limit the generalisability of the results. Nevertheless, this ethical requirement, and the subsequent limitation in terms of generalisability, applies to most studies on insight in psychosis.

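### Follow-up and censoring of one-year admissions and suicidal events are left open at 50% assumed drop-out, and suicidal events will be too few for the planned multivariable Cox model or for the claim made about suicide risk

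*Protocol article*

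**What the plan says.** Under Secondary outcomes, the Hospitalizations and Suicidal behaviour paragraphs define time to hospitalization, days in hospital, emergency mental-health presentations (for secondary analyses) and time to first attempt or completed suicide over one year. Neither paragraph names a data source. Reduced hospitalizations and lower suicide rates are hypotheses iii and iv in the Background.

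The Statistical analysis section prescribes multivariable Cox models for both outcomes, adjusted for baseline variables, which "will model time to the outcome event (i.e., first suicidal event or hospital admission, respectively) or the censoring date as appropriate". It defines intention to treat as all patients with baseline data.

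The Assessments section, on the visits at T0, T1 and T2, says: "Data on different variables will be collected at each of these assessments". It refers to Table 1, which is not shown.

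The power section says "we have conservatively assumed a much higher drop-out rate of 50" per cent, and that "the study will be carried out with an initial sample size of *N* = 252 patients". It sizes the trial on the SAI-E alone: no event rate, hazard ratio or power is given for admissions or suicidal events.

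The Discussion (Outcome measures) raises the question whether an insight-improving intervention "may reduce suicide risk (and improve mood) in psychosis, which will be properly investigated in this RCT".

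**The concern.** Two things are at stake.

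The first is capture. A time-to-event analysis over one year needs a known event status up to a known date for each patient. The plan allows for half the patients leaving, and the text says neither how their later admissions and suicidal events are found nor when their time at risk ends. If observation ends when they leave, events are missed. The trial's own premises make a link between leaving and risk plausible: Strengths and weaknesses ties low cooperativeness to poor insight, and the Background ties poor insight to poor outcome. Censoring of that kind need not be independent of the event.

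The second is the number of events. Suicidal events over one year in clinically stable outpatients are likely to be few. A Cox model with several baseline covariates is unstable on a handful of events, and a null result could be read as reassurance on the insight paradox that the Discussion sets out to test.

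**Working it through.** **Inputs from the protocol.** 252 randomised (126 per arm); 126 analysed; 50% drop-out; T1 at about 8 weeks; T2 at one year; two-sided 5% level. The protocol gives no event risk, hazard ratio or drop-out timing, so those below are assumptions shown over a range.

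**The plan's own figure.** There is none for events. The drop-out step reproduces: 126 / (1 − 0.5) = 252. I take 252 as given. (Whether 63 per arm follows from the SAI-E inputs is a separate question.)

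**Step 1: events missed if observation stops at drop-out, equal hazards.** Share missed ≈ drop-out fraction × average fraction of the year left.
- Drop-out uniform over the year: 0.5 × 0.5 = 25%.
- All leave at T1: 0.5 × (52 − 8)/52 = 42%.
- Extreme, all leave at day 0: 0.5 × 1 = 50%.

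**Step 2: drop-outs at k times the completers' hazard.** Let r be the completers' one-year risk and h = −ln(1 − r). Completers contribute 0.5(1 − e^(−h)) and drop-outs 0.5(1 − e^(−kh)), of which 0.5(1 − e^(−kht)) is seen by leaving time t (t = 8/52, or averaged over the year). The share missed is (drop-out total − seen) / (completers + drop-out total), for r = 5% (r = 20% in brackets):

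| k | Uniform drop-out | All leave at 8 weeks |
|---|---|---|
| 1 | 25% (24%) | 42% (42%) |
| 1.5 | 29% (28%) | 50% (48%) |
| 2 | 32% (30%) | 55% (52%) |
| 3 | 36% (32%) | 62% (57%) |

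The loss passes one half only when drop-out is early and drop-outs are also at higher risk.

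**Step 3: events and power.** Events = 252 × one-year risk. Power (Schoenfeld, 1:1) = Φ(√events × |ln HR| / 2 − 1.96). Example at 5% risk: 252 × 0.05 = 12.6; √12.6 × 0.693 / 2 = 1.23; Φ(1.23 − 1.96) = 23%. At HR 0.5:

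| Outcome, assumed risk | Full capture: events, power | 25% missed | 42% missed |
|---|---|---|---|
| Suicidal event, 2% | 5.0, 12% | 3.8, 10% | 2.9, 9% |
| Suicidal event, 5% | 12.6, 23% | 9.5, 19% | 7.3, 15% |
| Suicidal event, 10% | 25.2, 41% | 18.9, 33% | 14.6, 26% |
| Admission, 20% | 50.4, 69% | 37.8, 57% | 29.2, 47% |
| Admission, 30% | 75.6, 85% | 56.7, 74% | 43.8, 63% |

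For 80% power at HR 0.5, 66 events are needed: 4(1.96 + 0.84)² / (ln 0.5)² ≈ 65.3, rounded up.

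**Step 4: events per coefficient.** The number of covariates is not stated. Treatment plus two baseline variables, the fewest that the plural allows, makes three coefficients. Five events give 5/3 ≈ 1.7 per coefficient and 25 events give 25/3 ≈ 8.3.

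**Step 5: who is analysed.** Statistical analysis defines intention to treat as all with baseline data, which points to 252. The power section speaks of 126 patients analysed by intention to treat. If only 126 contributed, the suicidal-event counts at 2% to 10% would fall to 2.5 to 12.6, with 8% to 23% power at HR 0.5.

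**The case against.** A reader might infer that events are sought only at study visits, that most will therefore be lost, and that censoring is informative and will distort the hazard ratio. The documents do not support going that far.

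- No passage limits capture to visits. The Assessments sentence is general, Table 1 is not shown, and the full protocol or analysis plan may name the source and the censoring date. Bed-days and emergency presentations could well come from service records, and the Support group section says continuing care will help to identify adverse events.
- The 50% is a cautious planning figure for the SAI-E comparison, not an expected loss. The same section says: "Attrition rates in previous RCTs investigating MCT effects on symptoms were low (approximately 10" per cent. At 10% drop-out, Step 1 would give only 0.10 × 0.5 = 5% to 0.10 × 44/52 = 8.5% missed.
- A loss of most events needs early drop-out together with higher risk among those who leave.
- A biased hazard ratio would also need drop-out to differ by arm or to act differently in the arms. No such difference is stated, and the control group is designed to reach similar attendance. A Cox model keeps a drop-out's time until censoring, so counting completers alone would exaggerate both loss and bias.

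This all stands, and it makes the capture point conditional. It does not answer the event-count point, which assumes full capture of all 252. Nor is the event source purely an analysis-plan matter: whether patients who leave agree to record follow-up is best settled before enrolment, because an analysis plan cannot recover events that were never collected. The article describes itself as at a pre-recruitment stage. Health records are mentioned, but for the smartphone-platform and digital-biomarker work, not as the source of these outcomes.

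**Conclusion.** The point holds in two parts of different strength.

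**Conditional.** The text leaves the event source after drop-out and the censoring date undefined while allowing for 50% drop-out. If event follow-up ended at drop-out, 25% to 42% of events would be missed at equal hazards, more if drop-outs are at higher risk, and censoring may be informative. This rests on the 50% figure and on assumed drop-out timing. That follow-up does end there is not shown.

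**Unconditional on loss.** At assumed one-year risks of 2% to 10%, full capture of 252 patients gives about 5 to 25 suicidal events and 12% to 41% power to detect a halved hazard. A multivariable Cox model would be unstable, and the Discussion's statement about suicide risk is stronger than the design supports. The risks are assumptions, but 66 events would require a one-year risk of about 26% (66/252) even with complete follow-up.

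**What to change.** 1. **Event follow-up.** State that admissions, bed-days, emergency mental-health presentations and suicidal events are taken from hospital and clinic records to day 365 for every randomised patient who has not withdrawn consent to record use, whether or not T1 or T2 is attended. Censor only at day 365, at a death not counted as an event, on a move out of the catchment area, or on withdrawal of that consent. Say plainly that all 252 enter these analyses. The setting allows it: the clinic is linked to a publicly funded hospital, and the protocol says "most of our psychosis patients receive mental healthcare in our clinic with the exception of a tiny proportion". The cost is one record extraction by staff blind to allocation, and consent wording that separates leaving the visits or groups from leaving record follow-up, if it is not already there. Events outside the area may still be missed.

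2. **Suicidal events.** Replace the multivariable Cox model with counts per arm and exact confidence intervals. Add at most one penalised model (for example Firth) with a single pre-chosen covariate such as previous attempt, which is already collected at baseline. Call the outcome exploratory in Methods and Discussion, and state that a null result gives no reassurance. This costs only wording.
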